#### Exclusion criteria

Volunteers will be excluded if they report (1) medical conditions that can interfere with the outcomes of the intervention, e.g., diabetes, cancer, cardiovascular problems, or (2) ongoing psychotherapy.

### Recruitment

Recruitment will be conducted via the internet only. Advertisements concerning the project and invitations to take part in the study will be implemented using social media, targeting the Brazilian Portuguese speaking population. Additionally, participants of a previous online survey (SHER 1- study) who volunteered to participate in future studies will also be contacted.

### Participants’ information and consent

Written informed consent will be obtained electronically from all participants before any data collection ensues. The information and consent form will explain the objectives of the study, that there is no incentive for taking part, and that privacy and confidentiality is guaranteed as well as the right to withdraw from the study at any point in time without giving reasons or any negative consequences. There is no foreseeable risk associated with participation. Potential burdens from taking part in the study include the possible inconvenience from spending more time with one activity or feeling uncomfortable because of some questions or materials. In case participants would feel upset as a result of answering some of the questions or being involved in some of the intervention activities, they will have the opportunity to contact the research team, with or without disclosing their identity. In case of unexpected findings (for example concerning mental health), participants will be informed, supported, and guided by the research team.

If participants have any questions or wish to be informed of the results of the project and relevant publications, they are given with the opportunity to contact the principal investigator through the contact information provided in the online survey.

### Sample size

Considering the number of variables of the study (with a power of .80 or greater and with a significance level set at *α* = .05), the minimum sample size needed to find meaningful differences in sexual health is 102 participants (51 in the intervention and 51 the control group [26]). Considering gender differences, we will aim to obtain twice this sample size (*N* = 204), i.e., 102 participants per gender.

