Recently, two studies tested an in vivo transdiagnostic approach to sexual problems. Parsons et al. [13] conducted a pilot study with 13 HIV-positive gay and bisexual men reporting high rates of sexual compulsivity. After up to ten intervention sessions, improvements were observed in all psychological outcomes, including sexual compulsivity, depression, and anxiety, as well as decreases in drug use and HIV risk behaviors. Nonetheless, the initial small sample size (*n* = 13) and the fact that only 4 participants completed all sessions limit the conclusions that can be drawn from these results. De Ornelas Maia et al. [14] conducted an intervention to enhance quality of life and sexual functioning in unipolar depressive disorder or anxiety disorder participants. Both intervention groups (UP group intervention + pharmacological treatment, and pharmacological treatment only group) showed significant improvements in quality of life, anxiety, and depression. Improvements in sexual functioning was also noticed; the effect size was larger for sexual dysfunction in the non-depressed group (*d* = 2.62) than in the depressed group (*d* = 1.04).

Although progress has been made in the psychological treatment of sexual problems, feelings of shame in meetings with physical face-to-face contact limit their dissemination. In contrast, internet-delivered interventions may offer a greater degree of perceived privacy and, therefore, appeal to those who otherwise would avoid seeking help. Additional advantages of internet-delivered interventions concern their cost-effectiveness and accessibility [15] and the possibility for patients to deal with their problem in their home environment [16].

Internet-delivered psychological interventions vary in the way they are delivered. They are usually composed of a package of comprehensive self-help material with which the patient receives information and exercises on a weekly basis [17]. The content is delivered in the form of text, video, or audio, which is presented on a platform together with homework assignments and interactions with a clinician and/or automated support functions (i.e., self-guided treatments). Overall, there is evidence that I-therapy is more effective than no intervention and, more importantly, similar in efficacy to face-to-face treatments [18].

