### Data analysis

Data will be analyzed based on three measurements: baseline, end of intervention, and follow-up 6 months later. Analyses will be conducted to ascertain the balance on the measured covariates between the treatment and the control group.

To avoid potential post-treatment complications, such as noncompliance behavior after treatment assignment, the standard intention-to-treat estimate will be performed. To assess mean differences in the different domains (sexual health, emotion regulation, mental health, and sexual self-perception) over time and between groups, repeated-measures analysis of variance will be performed, with time (assessment point) as the within-subject factor, and intervention (group) as the between-subject factor. In case of violation of normality, changes over time in groups will be assessed with related-samples Wilcoxon tests. Multiple-imputation-based methods will be used to address missing data at follow-ups.

Intervention adherence will be monitored by the number of participants accessing the weekly training modules.

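### The recruitment target in each sex equals the stated minimum for .80 power, with no room for missing follow-up data, and the minimum rests on the number of variables, which cannot size a two-arm comparison

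*Protocol article*

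**What the plan says.** The Sample size section opens with "Considering the number of variables of the study", adds "with a power of .80 or greater" and "with a significance level set at *α* = .05", and concludes that "the minimum sample size needed to find meaningful differences in sexual health is 102 participants", split as "51 in the intervention and 51 the control group". It cites a reference for this. The target is then doubled to 204 on account of gender, "i.e., 102 participants per gender".

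Five other places bear on the point:

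- **Data analysis** plans an intention-to-treat repeated-measures ANOVA with time (three assessments) and group, and states that "Multiple-imputation-based methods will be used to address missing data at follow-ups".
- **Outcomes** defines the primary outcome as improvement in sexual health from baseline to the 6-month follow-up.
- **Sexual health**, under Measurements, gives women the FSFI and the female Sexual Quotient, and men the IIEF and the male Sexual Quotient.
- **Table 2, item 18** lists change in FSFI, IIEF and Sexual Quotient as primary outcomes, with the last assessment 8 months after baseline.
- **Table 2, item 16** gives the sample size as 102, not 204.

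**The concern.** A two-arm comparison is sized by the difference sought, its variability, the test, the error rates and the number expected to contribute data. The number of variables is not among these, so the stated basis cannot support the stated figure.

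The target in each sex is also the minimum itself. A minimum for .80 is the smallest size that reaches .80, so any loss of outcome data takes the comparison below it. The plan expects such loss and makes no allowance for it.

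At stake is how a null result is read. It would be set against a claim of 80% power or more, for a difference nobody has stated, in a sample smaller than the one the claim refers to.

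**Working it through.** **Inputs from the document.** Power .80, alpha .05, 51 per arm, 102 per sex. Effect size, SD, sidedness, within-person correlation and loss rate are not given. Below, d is a standardised difference, r the within-person correlation, and n the number per arm.

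**1. Can 102 be reproduced?** Not from the stated inputs. With assumed inputs, several routes come close:

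| Assumed route | Size for 80% power |
|---|---|
| Two-sample t-test, d = 0.5, one-sided 5% | 51 per arm (power 0.806) |
| Two-sample t-test, d = 0.5, two-sided 5% | 64 per arm |
| Overall F test in regression, f² = 0.15, 7 predictors (each sex completes 7 scales) | N = 103 |
| Between-group effect in repeated-measures ANOVA, f = 0.25, 3 visits | N = 86 at r = 0.5; 104 at r = 0.7 |

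Since different routes arrive near 102, the one actually used cannot be identified.

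**2. Effect of loss on the plan's own claim.** For a two-sided t-test, power is P(|T| > t_crit), with T noncentral t on 2n − 2 degrees of freedom and noncentrality δ = d√(n/2). Suppose 51 per arm gives exactly .80. Then δ = 0.5602 × √25.5 = 2.829, and with n retained δ becomes 2.829 × √(n/51).

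| Assumed loss | n per arm | δ | Power |
|---|---|---|---|
| 0% | 51 | 2.829 | 0.80 |
| 10% | 46 | 2.687 | 0.76 |
| 20% | 41 | 2.536 | 0.71 |
| 30% | 36 | 2.377 | 0.65 |

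The effect size drops out, because only the ratio n/51 changes δ. The test matters little: scaling the noncentrality of the time-by-group F test in the same way gives 0.75, 0.70 and 0.64.

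**3. Does doubling to 204 help?** Not on FSFI or IIEF. 204/2 = 102 per sex, and 102/2 = 51 per arm within sex.

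**4. Illustration at an assumed d = 0.5, two-sided, complete data.**

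- Single contrast at follow-up: δ = 0.5 × √25.5 = 2.525, power 0.71.
- Planned time-by-group F test, with equal correlation between visits and the difference present at both later visits: λ = n·d²/[3(1 − r)] = 51 × 0.25/[3(1 − r)] = 4.25/(1 − r), on 2 and 200 degrees of freedom. This gives λ = 6.07, 8.50 and 14.17, and power 0.58, 0.74 and 0.93, at r = 0.3, 0.5 and 0.7. Power reaches .80 at about r = 0.57.

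**5. Detectable difference at 80% power, two-sided 5%, per sex, for change from baseline to 6 months.** Change has SD σ√[2(1 − r)], so the detectable difference in units of σ is the t-test value (0.560, 0.626 and 0.670 for n = 51, 41 and 36) times √[2(1 − r)].

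| r (assumed) | Factor | No loss | 20% loss | 30% loss |
|---|---|---|---|---|
| 0.3 | 1.183 | 0.66 | 0.74 | 0.79 |
| 0.5 | 1.000 | 0.56 | 0.63 | 0.67 |
| 0.7 | 0.775 | 0.43 | 0.49 | 0.52 |

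**The case against.** The strongest reply is that the power claim cannot be checked, which is different from being false. The text speaks of meaningful differences and never of a medium effect; the derivation may stand in the cited reference or a fuller protocol. For a single two-sided contrast with complete data, 51 per arm reaches .80 from about d = 0.56. Repeated measures help as well: with baseline adjustment at r = 0.5, the detectable difference with complete data is about 0.49, which covers d = 0.5. All of this stands. A reader might infer from the 71% that the design fails at a medium effect, but d = 0.5 is an assumption, and the planned test runs from 58% to 93% over plausible correlations.

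A one-sided basis would explain 51 per arm. The planned ANOVA F test is non-directional, however, so it does not fit such a basis.

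Pooling the sexes would give 102 per arm and power of 0.94 at d = 0.5, or 0.84 after 30% loss. The document describes no pooled analysis, and FSFI and IIEF are completed by one sex only.

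On loss, a reader might cite the pilot in the Introduction in which "only 4 participants completed all sessions". That describes attendance in a small in vivo study, not loss to assessment, and under intention to treat non-adherent participants stay in the analysis. It supports no loss rate here. Imputation may recover some information from the end-of-intervention assessment, so the rates above are best read as effective loss. It does not bring back the full 51.

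That an article may leave detail to a fuller document does not answer the point. This article states a basis, a minimum and a target, and the target is exactly twice the minimum.

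**Conclusion.** The point holds in a limited form. The stated basis does not determine the sample size, and the target per sex carries no reserve for loss that the plan itself expects. If 51 per arm gives just .80, power is about 0.76, 0.71 and 0.65 at 10%, 20% and 30% loss. These loss rates are assumptions; the direction does not depend on the effect size. A minimum could exceed .80 slightly through rounding to whole participants (0.806 in the one-sided case), but not by enough to absorb such losses.

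The stronger statement, that .80 does not hold at a medium effect, is not supported. It depends on an effect size and a correlation that the document does not give.

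**What to change.** In the Sample size section, remove the clause on the number of variables and the claim to power above .80. Name the powered contrast: the group difference in change from baseline to 6-month follow-up, within each sex, two-sided 5%. Possible wording:

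*With 51 participants per arm in each sex and a two-sided 5% level, the group difference in change from baseline to 6-month follow-up is detectable with 80% power at about 0.56 SD with complete data and 0.63 to 0.67 SD with 20% to 30% loss, assuming a within-person correlation of 0.5. At a correlation of 0.3 these values are 0.66 and 0.74 to 0.79; at 0.7 they are 0.43 and 0.49 to 0.52. The correlation and loss rates are assumptions.*

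The sponsor should add the difference it regards as meaningful, so that these figures can be judged against it. The 204 in the Sample size section and the 102 in Table 2, item 16, must be reconciled.

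The cost is a restated paragraph with somewhat less favourable figures. The target of 204 does not change and no further participants are needed.

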## Methods

### Design

A randomized controlled trial will be conducted. Participants will be allocated to either group 1 (intervention) or group 2 (waitlist).

Randomization will be performed prior to the enrolment of study participants. Two separate block randomization lists will be created (one per sex) via sealed envelope and participants with baseline completed will be allocated either on the TREPS intervention group or to a waitlist control group. The allocation will be conducted by a clinical psychologist with no involvement in the project and the intervention provider will have no influence on participants allocation. Analyses will be conducted and presented following the Consolidated Standards of Reporting Trials (CONSORT) statement [24, 25].

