12. Intervention(s)	*Emotion regulation skills training*: The intervention will consist in an online emotion-regulation skills training for individuals with sexual problems. It will last for 8 weeks, encompassing psycho-educational and emotion-regulation skills components. Every week participants will gain access to a different intervention module of the training, containing videos, presentation slides, written support material, and a recommendation of activities to be completed until the following week of training. Participants are expected to dedicate 30 min to 1 h per week to complete each module.
13. Key inclusion and exclusion criteria	*Inclusion criteria for participants:* 1. Between 18 and 65 years of age. 2. Fluent in Brazilian Portuguese. 3. Self-reported sexual problems, assessed in men by a score of < 21 on the International Index Erectile Function (IIEF) and in women by a score of < 26 on the Female Sexual Function Index (FSFI). 4. In a stable relationship for at least the preceding 3 months. *Exclusion criteria for participants:* 1. Medical conditions that can interfere with the outcomes of the intervention, e.g., diabetes, cancer, and cardiovascular problems. 2. Ongoing psychotherapy.
14. Study type	Type: interventional Study design: - Allocation: randomized. - Intervention model: parallel assignment. - Masking: none (open label) - Primary purpose: treatment
15. Date of first enrolment	10 March 2021
16. Sample size	102
17. Recruitment status	Enrolling
18. Primary outcome(s)	- Change in Female Sexual Function Index (FSFI) at 6 months (time frame: baseline, 2 months after baseline (end of intervention), and 8 months after baseline (follow-up)). - Change in International Index of Erectile Function (IIEF) at 6 months (time frame: baseline, 2 months after baseline (end of intervention), and 8 months after baseline (follow-up)). - Change in Sexual Quotient (QS) at 6 months (time frame: baseline, 2 months after baseline (end of intervention), and 8 months after baseline (follow-up)).

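### The Sample size section plans 204 participants but Table 2 gives 102; if 102 were the total, power for the single-sex primary outcomes FSFI and IIEF would fall from .80 to about 50%

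*Protocol article*

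**What the plan says.** The Sample size section sets the design parameters "with a power of .80 or greater" and "with a significance level set at *α* = .05". It states that "the minimum sample size needed to find meaningful differences in sexual health is 102 participants", split as 51 and 51. It then continues: "Considering gender differences, we will aim to obtain twice this sample size", which it spells out as 204 in total and 102 of each gender.

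Table 2 (WHO trial registration dataset, under Ethics approval) reads "16. Sample size 102". Nothing marks this as a per-gender figure or as a minimum.

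Three other places bear on which number is needed:

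- Design: "Two separate block randomization lists will be created (one per sex"), so allocation is balanced within each sex.
- Measurements, Sexual health: women complete the FSFI and the female QS; men complete the IIEF and the male QS.
- Table 2 item 18: the primary outcomes are change in FSFI, in IIEF and in QS.

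**The concern.** The document gives two sizes for one trial, and the one in Table 2 is exactly half the one in the text. It also equals the minimum that the text gives for a single comparison before doubling, so the table may simply carry the wrong one of two figures.

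The choice matters because two of the three primary outcomes are single-sex scales. By the protocol's own reasoning, each needs 51 per arm within its sex. A trial that closed at 102 would agree with Table 2 and still miss the sample behind the stated power for FSFI and IIEF. Table 2 item 17 lists the trial as enrolling, so the point at which recruitment ends is still open.

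**Working it through.** **Inputs from the documents.** Alpha .05 and power .80 or greater (Sample size); 51 per arm for one comparison (Sample size); planned total 204 (Sample size); 102 in Table 2 item 16.

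**Inputs not in the documents, taken as assumptions.** Effect size, standard deviation and sidedness are not stated. I take a comparison of two means, two-sided, with power exactly .80, and show variants. For a total of 102 I assume an even sex split and then vary it.

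**Step 1: the plan's own figures.** The doubling is right: 2 × 102 = 204. The 102 itself cannot be reproduced, because no effect size is given. Solving backwards for the standardised effect d that 51 per arm detects:

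d = (z for alpha + z for power) × √(2/n)

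- Two-sided: (1.960 + 0.842) × √(2/51) = 0.555; with the t distribution, 0.560.
- One-sided: (1.645 + 0.842) × √(2/51) = 0.492; with the t distribution, 0.496. An assumed d of 0.5 tested one-sided with a t-test gives exactly 51 per arm.

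More than one set of assumptions is therefore compatible with 102, and the d values are only illustrative.

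**Step 2: sample per comparison if 102 is the total.** 102 / 2 sexes = 51 per sex; 51 / 2 arms = 25.5 per arm. That is half of the planned 51 per arm.

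**Step 3: power at half the sample.** Halving n divides the expected test statistic by √2, so the result follows from the planned power without knowing the effect size:

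power = Φ[(z for alpha + z for planned power)/√2 − z for alpha]

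| Case | Calculation | Power (normal) | Power (t) |
|---|---|---|---|
| Two-sided, planned .80 | Φ(2.802/1.414 − 1.960) | 0.508 | 0.500 |
| One-sided, planned .80 | Φ(2.486/1.414 − 1.645) | 0.545 | 0.540 |
| Two-sided, planned .90 | Φ(3.242/1.414 − 1.960) | 0.630 | 0.621 |

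**Step 4: precision and detectable effect.** The variance doubles, so the standard error and the confidence interval width rise by √2 = 1.41, or about 41%. The two-sided d detectable with 80% power rises from 0.555 to 0.785 (normal) or from 0.560 to 0.800 (t).

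**Step 5: uneven recruitment by sex** (total 102, two-sided, planned .80, normal approximation).

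| Split | Participants | Power, larger sex | Power, smaller sex |
|---|---|---|---|
| 50/50 | 51 and 51 | 51% | 51% |
| 60/40 | 61 and 41 | 58% | 43% |
| 70/30 | 71 and 31 | 65% | 34% |

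**Step 6: QS.** If male and female QS scores were pooled, a total of 102 would give 51 per arm, which is the stated minimum. If QS were analysed by sex, Steps 2 to 5 would apply to it as well.

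**The case against.** The strongest reply is that the only sample-size reasoning in the document leads to 204. Table 2 may just carry the stated minimum while the text carries the recruitment aim. On that view the power claim is sound and one table entry is mislabelled. This largely stands. It limits the point to a contradiction with a conditional consequence, but it does not remove the contradiction, because item 16 is presented as the size of the trial.

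The model is also open to challenge. The planned analysis is a repeated-measures analysis of variance, and the source for 51 per arm is a citation that is not shown. That is fair against the d values. The fall in power is less exposed, because it is scaled from the stated .80 rather than from an assumed effect, but it is worked out here for a simple two-group comparison.

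Several stronger readings are tempting, and the documents do not support them:

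- *The trial is planned at half its needed size.* The text plans 204.
- *Every primary outcome loses power.* QS is also primary, and the document does not say whether it is pooled across sexes.
- *Half the stated precision is lost.* No precision is stated, only power. The sample and the information halve; standard errors rise by 41%.
- *The registry entry is wrong.* Only Table 2 is shown, not the live record.
- *Reaching 204 would be an unplanned increase.* The text states the doubling and gives its reason.

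**Conclusion.** The contradiction is established: 204 in the Sample size section against an unqualified 102 in Table 2 item 16. It should be resolved, because recruitment could be closed on either figure.

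The statistical consequence is conditional. If 102 were the true total with an even sex split, FSFI and IIEF would each have about 25 to 26 per arm. Power would be about 50% two-sided, about 54–55% one-sided, or about 62–63% two-sided if the planned power was 90%. An uneven split would leave the smaller sex worse off. If 204 is the true target, this mismatch does not undermine the stated power.

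**What to change.** Reconcile the two places. The change that fits the protocol's own reasoning is to restate Table 2 item 16 as 204 (102 per sex) and to check that the registry record says the same. This corrects one table entry, and the registry if needed, and asks for no participants beyond the target already in the text.

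If 102 is the real total, amend the Sample size section instead. Withdraw the claim of .80 or greater for FSFI and IIEF, and restate the power or the detectable effect for each sex from the sponsor's own effect size, test and sidedness. As a guide only, under an assumed two-sided t-test the detectable d would move from about 0.56 to about 0.80. This costs a revised paragraph and the open acknowledgement that the single-sex comparisons have less power than now stated.
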